## Abstract

Convulsive status epilepticus (CSE) is a major medical emergency associated with a 50 % morbidity rate. CSE guidelines have recommended prompt management for many years, but there is no evidence to date that they have significantly improved practices or outcomes. Developing neuroprotective strategies for use after CSE holds promise for diminishing morbidity and mortality rates. Hypothermia has been shown to afford neuroprotection in various health conditions. We therefore designed a trial to determine whether 90-day outcomes in mechanically ventilated patients with CSE requiring management in the intensive care unit (ICU) are improved by early therapeutic hypothermia (32–34 °C) for 24 h with propofol sedation. We are conducting a multicentre, open-label, parallel-group, randomised, controlled trial (HYBERNATUS) of potential neuroprotective effects of therapeutic hypothermia and routine propofol sedation started within 8 h after CSE onset in ICU patients requiring mechanical ventilation. Included patients are allocated to receive therapeutic hypothermia (32–34 °C) plus standard care or standard care alone. We plan to enrol 270 patients in 11 ICUs. An interim analysis is scheduled after the inclusion of 135 patients. The main study objective is to evaluate the effectiveness of therapeutic hypothermia (32–34 °C) for 24 h in diminishing 90-day morbidity and mortality (defined as a Glasgow Outcome Scale score <5). The HYBERNATUS trial is expected to a decreased proportion of patients with a Glasgow Outcome Scale score lower than 5 after CSE requiring ICU admission and mechanical ventilation.

*Trial registration* Clinicaltrials.gov identifier NCT01359332 (registered on 23 May 2011)

## Background

Convulsive status epilepticus (CSE) is a life-threatening emergency that requires on-scene antiepileptic treatment adjusted according to the treatment response [1]. Hospital mortality is about 20 % overall and reaches 40 % in patients with severe refractory CSE [2]. The morbidity associated with CSE is more difficult to evaluate, as adverse events are often erroneously attributed to the cause of CSE. In retrospective studies, Glasgow Outcome Scale (GOS) scores indicated neurological impairments in 28 % of patients after CSE and 54 % after refractory CSE [3]. In a prospective multicentre study, 50 % of CSE survivors requiring ICU admission had impaired 90-day functional outcomes defined as a GOS score <5 [4]. By multivariate analysis, factors independently associated with poorer outcomes were age, duration of motor seizures, focal neurological signs, and progression to refractory status epilepticus (SE) [4]. Some of these factors may be amenable to improvement and therefore may constitute therapeutic targets. Thus, outcomes may be improved by the rapid control of seizure activity (shorter seizure duration and prevention of refractory CSE and NCSE) and by treatment of the cause of CSE [5, 6].

Therapeutic hypothermia has shown both anticonvulsant and neuroprotective properties after SE in experimental studies. In rats, hypothermia at 32–34 °C decreased the incidence of both seizures and associated local and hippocampal neuronal damage [7–13]. In humans, therapeutic hypothermia has been described merely as an adjuvant treatment of super-refractory SE in adults and paediatric patients [14–17]. Finally, therapeutic hypothermia may also target some of the causes of status epilepticus such as ischaemic or haemorrhagic stroke [18–22] and subarachnoid haemorrhage [23–25]. Its use in patients with traumatic brain injury demonstrated conflicting results [26–30]. Thus, pathophysiological considerations and experimental data suggest a beneficial effect of therapeutic hypothermia in SE. Proof of such an effect in human patients has not been obtained [31, 32].

The main goal of the HYBERNATUS trial is to determine whether therapeutic hypothermia (32–34 °C) for 24 h has neuroprotective effects compared to standard care alone. HYBERNATUS is a multicentre, open-label, parallel-group, randomised, controlled trial in patients with CSE requiring admission to the intensive care unit (ICU) and mechanical ventilation.

## Methods/design

### Ethical aspects

The study protocol was approved by the local independent ethics committee (Comité de Protection des Personnes CPP Ile de France IV, Saint Louis, on 1 September 2010, #2010/27) and the competent French health authorities (AFSSAPS, on 22 June 2010, #EudraCT 2010-A00466-33). Informed consent is obtained from each patient or next of kin prior to study inclusion. The trial was registered at Clinicaltrials.gov identifier NCT01359332 (registered on 23 May 2011).

### Aims

The main study objective is to evaluate the effectiveness of therapeutic hypothermia (32–34 °C) for 24 h in decreasing 90-day morbidity and mortality, defined as a GOS score <5, in patients with CSE requiring ICU admission and mechanical ventilation.

The secondary objectives are to evaluate the effectiveness of therapeutic hypothermia (32–34 °C) for 24 h in decreasing seizure duration, progression to refractory CSE, ICU mortality, hospital mortality, 90-day mortality, hospital stay length, and 90-day functional impairments (motor and/or cognitive impairment, epilepsy).

### Design

HYBERNATUS is a multicentre, open-label, parallel-group, randomised, controlled trial in patients with CSE requiring ICU admission and mechanical ventilation. Patients are allocated at random to either early therapeutic hypothermia plus standard care or standard care alone at the acute phase of ICU management.

### Setting

Among the 11 French ICUs participating in the study, 6 are in university hospitals. All participating ICU staff members have received training in the study procedures and in protocols for optimal CSE management.

### Study population

Inclusion criteria are age over 18 years, admission to one of 11 participating ICUs, CSE (5 min or more of continuous clinical seizure activity or more than two seizures without a return to baseline in the interval), time since seizure onset no longer than 8 h, and need for mechanical ventilation.

Exclusion criteria are a full recovery, need for emergent surgery (neurosurgery or other) precluding therapeutic hypothermia, postanoxic status epilepticus, dying patient, decision to withdraw or withhold life-sustaining treatments, and pregnancy.

All patients admitted to one of the participating ICUs with any seizure activity are screened for eligibility by the ICU physicians 24/7.

### Randomisation

Consecutive eligible patients are randomly allocated in a 1:1 ratio to one of the two treatment groups. The randomisation scheme involves permuted blocks and stratification on centre, age (≤65 or >65 years), and seizure duration (≤60 min or >60 min). Randomisation and concealment are ensured by using a secure, computer-generated, interactive, response system available at each study centre and managed by the biometrics unit of the Saint Louis University Hospital (Paris, France), which has no role in patient recruitment.

### Study interventions

The study protocol and randomisation arms are detailed in Figs. 1 and 2 and Table 1.

**Fig. 1 Fig1:**
[figure not shown]
HYBERNATUS trial diagram. *ICU* intensive care unit. *EEG* electroencephalogram

**Fig. 2 Fig2:**
[figure not shown]
Eligibility criteria, inclusion, randomisation, and treatment implementation modalities in each arm of the trial

**Table 1 Tab1:** HYBERNATUS trial flow chart

	Inclusion	Day 0	Day 1	Day 2 Day 7 Day 14 Day 28	ICU discharge	Hospital discharge	Day 90 (±7 days)
Eligibility: check inclusion and non-inclusion criteria	X						
Patient/next of kin information and consent	X						
Randomisation (within 8 h after CSE onset)		X					
Standardised anticonvulsant treatment		X					
Brain imaging and other aetiological investigations		X					
Therapeutic hypothermia (in the intervention group)		X	X				
Core temperature monitoring (every 4 h)		X	X				
Continuous EEG monitoring		X	X				
30-min continuous EEG extract (centralised reading)		X	X				
Clinical and laboratory monitoring		X	X	X	X		
Serious adverse event reporting		X	X	X	X	X	X
Glasgow Outcome Scale (GOS) score evaluation					X	X	X^1, 2^
Standard EEG							X^2^
Brain MRI							X^2^
MMSE score							X^2^
FIM scale score							X^2^
Neurological evaluation							X^2^

^1^By phone interview in all cases

^2^Neurologist visit, if feasible

### Standardised anticonvulsant treatments after randomisation in both groups

To be eligible, patients should have received at least one of the first-line anticonvulsant drugs (clonazepam and diazepam) listed in French guidelines. Patients with ongoing motor seizures who have not received a second-line anticonvulsant (fosphenytoin, phenytoin, phenobarbital, or sodium valproate) before randomisation receive a loading dose of one of these drugs selected according to the indications and specific contraindications of each [33].

Patients with refractory CSE, defined as CSE persisting despite two lines of anticonvulsant therapy within 60 min, are given an intravenous 2 mg/kg propofol bolus followed by an additional intravenous 1 mg/kg bolus every 5 min until motor seizures stop, at which point a continuous intravenous propofol infusion is started at a rate of 2–5 mg/kg/h. In patients with uncontrolled refractory CSE despite continuous intravenous propofol at a rate of 5 mg/kg/h, anaesthetic drugs (midazolam or thiopental) can be added.

CSE must be controlled within 60 min after randomisation in both groups and before the induction of therapeutic hypothermia in the experimental group.

### Therapeutic hypothermia group

The objective is to lower the core body temperature to 32–34 °C rapidly after randomisation and then to maintain this temperature for 24 h. The management in the therapeutic hypothermia group will include the following:sedation with propofol in a 1–2 mg/kg bolus followed by a maintenance infusion at a rate of 2–5 mg/kg/h; patients with refractory CSE before randomisation receive the propofol infusion rate that was required to stop the motor seizures;neuromuscular blockade with a 0.15 mg/kg bolus of cisatracurium or of another neuromuscular blocker followed by doses at 4-h intervals adjusted to maintain the response to train-of-four stimulation at two of four twitches;hypothermia induction with ice-cold intravenous fluids at 4 °C and then hypothermia maintenance with ice packs at the groin and neck and a cold-air tunnel around the patient’s body;after 24 h of hypothermia, passive rewarming by covering the patient with a warm blanket, at a slow rate of 0.25–0.5 °C per hour to avoid haemodynamic instability, cisatracurium is discontinued when normothermia is achieved; when the train-of-four response is four twitches, the propofol is stopped or decreased to the lowest dose needed to ensure tolerance of the endotracheal tube;If continued sedation is required, the choice of the sedative is at the discretion of the bedside physician, but propofol is not used for longer than 48 h;Core body temperature is monitored using an oesophageal probe throughout the therapeutic hypothermia phase and then during rewarming until two values 4 h apart are between 37° and 38° C.

### Control group

The bedside physician decides whether sedation should be initiated and maintained. If sedation is given, the same propofol regimen as in the therapeutic hypothermia group is used (1–2 mg/kg bolus and then 2–5 mg/kg/h intravenous infusion rate). If sedation is inadequate with continuous intravenous propofol 5 mg/kg/h, benzodiazepines may be added. Finally, if sedation must be maintained beyond 48 h, the propofol must be stopped and an anaesthetic selected by the bedside physician given instead.

### General management of convulsive status epilepticus (CSE) in both groups

In both control and intervention groups, a continuous EEG monitoring is started within 2 h after randomisation and maintained during the first 48 h after randomisation and/or until body temperature normalisation in the therapeutic hypothermia group. A 30-min standard EEG extracted from the continuous EEG recording is sent for centralised interpretation by a qualified neurophysiologist within 2 h after the initiation of continuous EEG monitoring. If the results show refractory CSE or progression to NCSE, the patient is given a 2-mg/kg propofol bolus, repeated every 5 min if necessary, and then a maintenance intravenous infusion at 2–5 mg/kg/h to obtain and maintain a burst-suppression EEG pattern for 24 h. Further EEG epochs are sent for centralised interpretation by a qualified neurophysiologist until a burst-suppression EEG pattern is observed.

Second-line anticonvulsant drugs administered intravenously are switched to enteral administration when feasible. Patients with a known history of epilepsy are given their previous treatment enterally or parenterally. Aetiological investigations are carried out early, simultaneously with the symptomatic and anticonvulsant treatment. They include a thorough initial physical examination and tests for metabolic disturbances (e.g. hypoglycaemia, hypocalcaemia, hyponatraemia, uraemia, hypomagnesaemia, hypoxaemia, and hypercapnia) and carbon monoxide poisoning. Computed tomography (CT) of the brain is performed routinely. In patients with previously treated epilepsy, serum anticonvulsant drug assays are performed if appropriate, to determine whether levels are within the therapeutic range. As dictated by the clinical setting, tests are performed for disorders such as porphyria and thyroid dysfunction and/or for toxic substances (alcohol, cocaine, amphetamines, tricyclic, or serotonergic antidepressants). A lumbar puncture is performed in patients with any of the following: fever, meningeal neck stiffness, immunodeficiency, and negative findings from the other aetiological investigations. Magnetic resonance imaging (MRI) may be considered if all other aetiological investigations are negative [34].

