### Safety and potential risks associated with the study

Rigorous monitoring procedures are implemented to minimise the risks associated with therapeutic hypothermia in patients after CSE. Continuous EEG monitoring is performed for 48 h after inclusion, and a 30-min EEG extract is interpreted centrally before implementation of the randomly allocated treatments. Although neuromuscular blockade can theoretically mask recurrent seizure activity, this risk is lessened by the anticonvulsant properties of therapeutic hypothermia.

Preliminary data show that 82 % of patients admitted to the ICU for CSE receive mechanical ventilation for longer than 24 h, and that nearly 25 % of those given mechanical ventilation for less than 24 h have a 90-day GOS score lower than 5. Thus, the use of mechanical ventilation for an unnecessarily long period seems very rare. No criteria are available for predicting which patients will require mechanical ventilation for less than 24 h. Finally, this study includes only patients with severe CSE requiring both ICU admission and mechanical ventilation.

Patients receiving therapeutic hypothermia and/or propofol are closely monitored for adverse effects of these treatments such as infections and propofol infusion syndrome. We therefore believe that the use of therapeutic hypothermia does not expose the patients to undue risks, given the high morbidity and mortality rate in our prospective study [4] and the safety measures included in the HYBERNATUS trial protocol.

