#### Secondary outcomes

The method described above for the primary outcome will also be used for the percentages of patients with EEG evidence of an ongoing epileptic seizure between 6 and 12 h or of refractory SE after randomisation; ICU, hospital, and 90-day mortality; and 90-day functional impairments.

To compare seizure duration (in minutes), we will build a semi-parametric regression model (Cox or Fine–Gray) appropriate for an analysis of competing risks (control of SE vs. death without control of SE). This approach will be used also for ICU and hospital stay lengths (alive at ICU or hospital discharge vs. death in the ICU or hospital, respectively).

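### The continuous EEG stopping rule depends on arm and EEG-evidenced refractory status epilepticus has no closing time, so this secondary outcome may be compared over unequal detection windows

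*Protocol article*

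**What the plan says.** All references are to the protocol article.

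- **EEG duration, general management section.** Recording starts within 2 h of randomisation in both groups and is "maintained during the first 48 h after randomisation and/or until body temperature normalisation in the therapeutic hypothermia group". The second stopping condition applies to one arm only.
- **EEG duration, safety section.** "Continuous EEG monitoring is performed for 48 h after inclusion", with no mention of arm.
- **Refractory SE.** The outcome list gives a percentage of patients with no period attached. The secondary-outcome paragraph under Statistical methods applies logistic regression to EEG evidence of ongoing seizure between 6 and 12 h "or of refractory SE after randomisation". The first item in that sentence has a window and the second has none.
- **Cooling timetable.** The target is to be reached "rapidly after randomisation and then to maintain this temperature for 24 h". The next step is "after 24 h of hypothermia, passive rewarming by covering the patient with a warm blanket". The speed set for this step is "at a slow rate of 0.25–0.5 °C per hour to avoid haemodynamic instability".
- **Seizure duration.** It is analysed as time to control of SE, with death without control as the competing event. Onset and control times are collected, and so are EEG start and stop times (Data collection and follow-up).

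**The concern.** After randomisation, the general management section relies on EEG to show refractory convulsive SE or progression to non-convulsive SE. A non-convulsive event can be counted only while EEG is running. If the recording stops at a time that depends on arm, and the outcome is counted for as long as recording lasts, the chance of being classified as refractory depends on arm even when the true risk is equal. A shorter hypothermia window would favour hypothermia, and a longer one would count against it.

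Progression to refractory convulsive SE is a named secondary objective, and an anticonvulsant effect of cooling is part of the rationale. A detection artefact could imitate or hide that effect.

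The hours in question may also be unusual ones. In the hypothermia arm the neuromuscular blocker is stopped at normothermia and propofol is reduced or stopped afterwards. If recording ended at normothermia, it would end just as blockade and sedation are withdrawn, while controls were still being recorded.

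**Working it through.** The plan gives no figure for this outcome. The only design figure used below is 135 per group. It reproduces: 40% against 60%, two-sided 5%, 90% power gives 130 per arm without continuity correction. An assumed factor of about 1.007 for one O'Brien-Fleming interim gives 130 × 1.007 = 130.9, so 131, within 3% of 135. The sample size is not at issue.

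**1. When does the hypothermia arm reach normothermia?**

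Hours from randomisation = c + k + 24 + (37 − θ)/r

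- c, time to control of SE before cooling: 0–1 h, from "CSE must be controlled within 60 min after randomisation in both groups and before the induction of therapeutic hypothermia in the experimental group"
- k, time to reach target temperature: not stated; assumed 0–8 h
- 24 h of maintained hypothermia
- θ, temperature held: 32 or 34 °C; r, rewarming rate: 0.25 or 0.5 °C/h
- 37 °C as normothermia: the lower end of the range at which the protocol ends temperature monitoring

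Rewarming takes (37 − 34)/0.5 = 6 h to (37 − 32)/0.25 = 20 h.

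| Cooling time k | Earliest | Latest |
|---|---|---|
| 0 h | 0 + 0 + 24 + 6 = 30 h | 1 + 0 + 24 + 20 = 45 h |
| 4 h | 0 + 4 + 24 + 6 = 34 h | 1 + 4 + 24 + 20 = 49 h |
| 8 h | 0 + 8 + 24 + 6 = 38 h | 1 + 8 + 24 + 20 = 53 h |

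The overall range is 30–53 h. If normalisation means the temperature-monitoring criterion of two values 4 h apart between 37 and 38 °C, up to 4 h is added (to 57 h at the top).

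**2. Difference from 48 h in controls**

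- Clause read as *or*, with recording allowed to stop at normothermia: as early as 30 − 48 = −18 h.
- Clause read as *and* (the later of the two times): 0 to 53 − 48 = +5 h.
- Safety section taken alone: 0 h.

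**3. What could that do to the outcome?** Assume no treatment effect, and that the whole hypothermia arm stops at the stated hour. The proportion detected by 48 h, p, is not in the documents; take 20%, with 10% and 30% as a range.

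Constant rate: detected by T = 1 − (1 − p)^(T/48).

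Events early (assumed 12 h time constant): detected by T = p × (1 − e^(−T/12))/(1 − e^(−4)).

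| p by 48 h | Constant, 30 h | Constant, 53 h | Early, 30 h | Early, 53 h |
|---|---|---|---|---|
| 10% | 6.4% (−3.6) | 11.0% (+1.0) | 9.4% (−0.6) | 10.1% (+0.1) |
| 20% | 13.0% (−7.0) | 21.8% (+1.8) | 18.7% (−1.3) | 20.1% (+0.1) |
| 30% | 20.0% (−10.0) | 32.6% (+2.6) | 28.1% (−1.9) | 30.2% (+0.2) |

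Brackets give the spurious difference in percentage points, hypothermia minus control.

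For scale, the standard error of the difference at 20% with 135 per arm is √(2 × 0.2 × 0.8/135) = 4.9 points. At the middle of the range, (30 + 53)/2 = 41.5 h, the constant-rate figure is 1 − 0.8^(41.5/48) = 17.5%, or −2.5 points.

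**The case against.** **The safety section gives everyone 48 h.** The natural joint reading is 48 h for all, extended when a cooled patient is not yet normothermic. This is a fair reading, and under it the negative differences vanish, leaving 0 to about +2 points at 20%. But the printed clause also permits stopping at normothermia, so the mismatch stands. A reader might infer that the arms *are* compared over different windows. The documents support only that they may be.

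**Seizure duration is not open-ended.** A reader might infer that total seizure duration shares the defect, since the outcome list gives it no cut-off. The analysis text ends it at control of SE or at death without control, and control is required within 60 min of randomisation, before cooling. An EEG stop 30–53 h later has little bearing on that. Only recurrences after control and the censoring time are left open, and a fuller document may settle those.

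**Refractory SE is mostly an early classification.** It is defined by persistence despite two lines of therapy within 60 min. Both arms start EEG within 2 h, and an extract goes for central reading within 2 h of that start. This stands as a reason to expect a small artefact. It does not remove the issue, because the 60 min defines refractoriness and not the period in which it may be found, and further EEG epochs can be read.

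**The size is built on assumptions.** This is true of the event rate, cooling time and time pattern, and the −7 needs a whole arm to stop at the earliest hour. The constant-rate figures are not a strict limit either: if events clustered after rewarming, stopping early would lose more.

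**A condensed article leaves windows to fuller documents.** This is fair for a missing window alone. Here the article prints an arm-specific EEG rule, a conflicting flat rule, and an outcome counted from that EEG without an upper limit. Followed as written, these permit unequal observation.

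**Conclusion.** The point holds for one secondary outcome, EEG-evidenced refractory SE. The general management and safety sections do not agree on how long EEG runs, only the hypothermia arm has the extra stopping condition, and the outcome has no closing time. The hypothermia window could be up to about 18 h shorter than the controls' 48 h under *or*, and equal to about 5 h longer under *and*, taking cooling to last 0–8 h.

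With 20% detected by 48 h, the spurious difference is about −7 to +2 points at a constant rate and about −1 to 0 if events come early. Its direction depends on which reading was followed. The upper part of that range exceeds one standard error (4.9 points), enough to colour the interpretation of this outcome, but it needs the *or* reading, early stopping throughout the arm and a steady event rate. A smaller effect is more plausible.

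The documents do not support extending this to the primary outcome (90-day Glasgow Outcome Scale score by blinded phone interview), to the 6–12 h seizure outcome, which lies inside EEG cover in both arms, or to time to control of SE.

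**What to change.** 1. Reconcile the general management and safety sections on when continuous EEG ends in each arm, and state which rule was applied. This review takes no position on which is right.
2. In the logistic regression, count EEG-detected refractory SE only within one post-randomisation window that EEG covers in both arms: for example to 48 h, or a shorter time if recordings ended earlier. Choose it from the recorded EEG start and stop times, without looking at events by arm.
3. As a sensitivity analysis, use time to first detection, censored at EEG stop, with death as a competing event. Such censoring does not fit the logistic model, so it should be a separate analysis. The competing-risks approach planned for other secondary outcomes can be reused.
4. List later EEG events by arm descriptively, and report EEG duration by arm.

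**Cost.** No new data are needed, since EEG start and stop times are already collected, and patient care does not change. The article reports enrolment complete and analysis ongoing, so the work is an outcome definition plus one extra model. The small downside is that late EEG events, including some around slow rewarming, leave the main comparison.
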